### Intervention description {11a}

#### Patient-tailored PROfeel lifestyle advice

The RCT starts with a 4-week ESM assessment (see Table 1 for timeline). ESM is an innovative, validated, structured diary technique for longitudinal measurements of fluctuating states, that captures life as it is lived on the spot [22, 23, 29]. Multiple ESM applications are available for smartphones. In this study, we use the Ethica application (www.ethicadata.com) in which participants complete ESM surveys (i.e., diaries) approximately 5 times per day. In a first step, ESM data are used by a statistician to compute an individual descriptive report and an individual dynamic report with fatigue-perpetuating dynamic networks, identifying the contemporaneous and time-lag relations between fluctuations in fatigue and behavior, sleep, social context, cognitions, and feelings [23]. In a next step, the investigator uses the descriptive and dynamic reports to produce a reduced PROfeel report. Face-to-face, the investigator and participant discuss the PROfeel report and use shared decision-making to formulate a patient-tailored lifestyle advice. The term “lifestyle” here refers to an area of daily life that can be modified to potentially reduce fatigue and/or improve quality of life and self-efficacy. The combination of ESM with personalized feedback, leading to patient-tailored lifestyle advices, is named PROfeel. Details follow in the sections underneath.

**Table 1 Tab1:** Participant timeline in QFS-study

Week	Activity	Description
0	Screening	Evaluation of participant’s eligibility for the QFS-study by social pediatrician (and pediatric immunologist/rheumatologist in case of JIA diagnosis).
1	Study visit T0	Participant completes baseline KLIK questionnaires and installs the PROfeel app on smartphone to start ESM measurement. Participant also starts weekly measurement (of fatigue, quality of life, and self-efficacy) on smartphone which lasts throughout the study.
1-4	ESM phase I	Participant starts 4 weeks of ESM, with 5 surveys to answer per day. Surveys contain items inquiring after, e.g., fatigue and other symptoms, (social) activities, and affect in the last 3 h.
5	Study visit T1	Participant completes T1 KLIK questionnaires and is randomly allocated to either 12 weeks of patient-tailored PROfeel lifestyle advice or generic dietary advice. Biological samples (i.e., blood, stool, saliva, and hair) are collected for the first time.

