5-16	Intervention I	Participant adheres to allocated advice for 12 weeks. To improve adherence, participant receives a boost from the investigator by phone and/or mail.
17	Study visit T2	Participant completes T2 KLIK questionnaires and evaluates first intervention with investigator. Biological samples (i.e., blood, stool, saliva, and hair) are collected for the second time.
17-20	ESM phase II	Participant starts a second period of 4 ESM weeks, with 5 surveys to answer per day. Survey items are identical to ESM phase I.
21	Study visit T3	Participant completes T3 KLIK questionnaires and is allocated to the other intervention arm (either 12 weeks of patient-tailored PROfeel lifestyle advice or generic dietary advice).
21-32	Intervention II	Participant adheres to allocated advice for 12 weeks. To improve adherence, participant receives a boost from the investigator by phone and/or mail.
33	Study visit T4	Participant completes T4 KLIK questionnaires and evaluates second intervention with investigator. If fatigue remains severe, participant can be referred to ECCF for post-trial care. Biological samples (i.e., blood, stool, saliva, and hair) are collected for the third time.
33-60	Follow-up	Weekly measurement (of fatigue, quality of life, and self-efficacy) on smartphone continues until 12 weeks after T4. During week 60, participant completes follow-up KLIK questionnaires, marking the end of QFS-study participation.

Healthy controls only have one study visit during which questionnaires (i.e., baseline KLIK, Eetscore, and optionally Food Frequency Questionnaire) and biological samples (i.e., blood, stool, saliva, and hair) are collected

*ESM* experience **s**ampling methodology, *CIS-8* Checklist Individual Strength-8 questionnaire, *ECCF* Dutch Expert Centre for Chronic Fatigue

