#### PROfeel: ESM assessment

The ESM surveys are structured within the framework of the biopsychosocial model [16, 17], meaning that all surveys consist of a fixed set of items regarding potentially fatigue-perpetuating factors of biological, psychological, and social nature. These factors are part of the theoretical framework of efficacious elements of CBT [18]. Next to the fixed set, participants can add personalized items of their choice. These items represent additional somatic symptoms, symptom-related behaviors, feelings and cognitions, and a self-selected factor. This way, participants receive personalized surveys. Depending on the personalization, the surveys consist of 12 to 21 items. All items (e.g., “in the last 3 hours, I was fatigued”) are answered on a visual analogue scale (VAS) scale ranging from “not at all” to “very much”. Completing the personalized survey takes approximately 1 min. The ESM content was developed in an interdisciplinary team of researchers and clinicians and was previously tested in a feasibility study [23].

With regard to compliance, participants are asked to respond to at least 100 out of 140 ESM surveys (i.e., ≥70% compliance) to allow the computation of a reliable descriptive report and a reliable dynamic report with fatigue-perpetuating dynamic networks. PROfeel uses a time-based ESM recording method with interval contingency, meaning that all surveys are distributed at a fixed interval of 3 h. To allow for the highest compliance, participants are asked during the intake to select at what time slots they would like to receive their surveys (e.g., starting at 9 AM, 10 AM, or 11 AM each day).

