#### PROfeel: feedback report and shared decision-making

After the ESM assessment, the investigator and statistician independently select which figures from the descriptive and dynamic reports should be discussed with the participant. This selection is based on statistical significance and relevance (i.e., weight and context of the dynamic network factor loadings, potential contribution to the patient’s self-knowledge, and usefulness as input for patient-tailored PROfeel lifestyle advice) and compiled into a PROfeel report. During a face-to-face meeting, the investigator discusses the PROfeel report with the participant. Input from the participant is leading for the interpretation of the figures. Participants are always asked to indicate the extent to which they recognize themselves in each figure. Two example figures are shown in the Additional files 1 and 2 (Figs. 1 and 2). Patients have considered the visual presentation of their symptoms a strong feature of PROfeel [23].

Once the PROfeel report is discussed, the investigator and participant decide what type of personalized lifestyle advice might help to reduce fatigue severity and/or improve quality of life and self-efficacy in daily life. This advice can be based directly on the figures from the PROfeel report, but may also be linked to something that came up during the meeting. Thus, the PROfeel report is used as a clinical conversation tool to create patient-tailored lifestyle advices. The report is not intended to be the sole input for lifestyle advices.

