## Statistical methods

### Statistical methods for primary and secondary outcomes {20a}

To evaluate on the group level the effectiveness of the patient-tailored PROfeel lifestyle advices against generic dietary advices in reducing “fatigue severity” and improving “quality of life” and “self-efficacy” (objective 1), two statistical tests will be performed. The first test, is a 2 × 2 ANCOVA with “fatigue severity” at T2 as dependent variable, “fatigue severity” at baseline as covariate, and intervention condition as fixed factor. This test is used to compare the reduction in “fatigue severity” for the PROfeel-first group against the dietary-first group. The second test is a repeated measures 2 × 2 ANOVA to test whether the order in which participants received the advices is of relevance. The same tests will be performed for secondary outcomes “quality of life” and “self-efficacy”.

To evaluate the effectiveness of the patient-tailored PROfeel lifestyle advices and generic dietary advices in reducing “fatigue severity” and improving “quality of life” and “self-efficacy” at the individual level (objective 2), the permutation distancing test (PDT) will be used. This test is currently under development (see supplement of 41). This test takes into account autocorrelation, handles missing data by making optimal use of all observations, and is specifically developed for *N*=1 designs with a fixed intervention start.

To explore individual effects on pre-post intervention change in the dynamic networks for the participants who first receive patient-tailored PROfeel lifestyle advices first (objective 3), single-subject residual dynamic structural equation modelling (RDSEM) [40] will be used in Mplus. We will model the pre- and post-intervention dynamic networks in one SEM model [41]. This allows for statistical testing of the differences between the pre- and post-network estimates.

To explore the biological profile of adolescents and young adults with QFS and compare it with participants with CFS/ME and JIA, as well as healthy controls (objective 4), we will use between-group ANOVAs and/or linear regression analyses.

Exploration of the relationship between individual differences in “fatigue severity” improvement and biological profile changes pre-post interventions (objective 5) will be conducted with growth mixture modelling (GMM) [42] in Mplus.

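### Objective 3 has no comparator, and links chosen from ESM phase I for significance or weight will on average appear weaker in phase II without any true change

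*Protocol article*

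**What the plan says.** The section on the PROfeel feedback report and shared decision-making states who makes the choice and when: "After the ESM assessment, the investigator and statistician independently select which figures from the descriptive and dynamic reports should be discussed with the participant". On the criterion: "This selection is based on statistical significance and relevance (i.e., weight and context of the dynamic network factor loadings", with contribution to self-knowledge and usefulness for the advice also listed. Of the resulting advice it says "This advice can be based directly on the figures from the PROfeel report", but also "The report is not intended to be the sole input for lifestyle advices".

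Table 1 has two ESM periods. In weeks 1 to 4, "Participant starts 4 weeks of ESM, with 5 surveys to answer per day"; in weeks 17 to 20, "Participant starts a second period of 4 ESM weeks, with 5 surveys to answer per day. Survey items are identical to ESM phase I". Both arms complete both periods.

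For objective 3, {20a} restricts the network comparison to participants who receive PROfeel first. It fits both networks in one single-subject residual dynamic structural equation model and states: "This allows for statistical testing of the differences between the pre- and post-network estimates". It describes no comparison arm, no links named in advance and no allowance for selection.

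**The concern.** For a PROfeel-first participant, phase I does two jobs. It supplies the figures from which the advice may be built, and it is the only possible pre-intervention network. An estimate that comes forward because it is large or significant tends to exceed the true value. The phase II estimate of the same link has not been selected, so on average it is lower even if nothing has changed.

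Objective 3 asks through which mechanisms PROfeel worked. The natural place to look is the links that the advice acted on, and those are the links most exposed to this regression to the mean. With no comparator, a real weakening and an artefact of selection cannot be told apart.

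**Working it through.** **Plan's own figure.** 4 weeks × 7 days × 5 surveys = 140, and 100/140 = 71.4%. This agrees with "participants are asked to respond to at least 100 out of 140 ESM surveys (i.e., ≥70% compliance".

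**Inputs from the article.** n = 100 to 140 surveys per phase. Surveys have 12 to 21 items; with fatigue as one of them, K = 11 to 20 candidate links with fatigue.

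**Assumptions, not in the article.** True standardised links b are normal with mean 0 and SD τ = 0.05 to 0.15. Each phase estimate is b plus independent error with variance s² = 1/(n − K − 2). A link is selected if |z| > 1.96 in phase I, and the strongest such link is taken. There is no true change.

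**Expected fall.** Given the phase I estimate e₁, the mean of b, and hence of the phase II estimate, is e₁ × τ²/(τ² + s²). Selection uses phase I only, so the proportional fall is s²/(τ² + s²).

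- Mildest corner (K = 11, n = 140, τ = 0.15): s² = 1/127 = 0.00787; fall = 0.00787/(0.0225 + 0.00787) = 26%.
- Middle (K = 11, n = 140, τ = 0.10): fall = 0.00787/(0.0100 + 0.00787) = 44%.
- Severest corner (K = 20, n = 100, τ = 0.05): s² = 1/78 = 0.01282; fall = 0.01282/(0.0025 + 0.01282) = 84%.

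**Single-subject test.** Take z = (e₁ − e₂)/(s√2), signed so that e₁ is positive, and test two-sided at 5%. In simulation over the same grid, the strongest selected link is called significantly weaker in about 9 to 29% of cases, against a nominal 2.5% in that direction. It is called significantly stronger in under 0.3%.

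**Check with a time-series model.** Lag-1 vector autoregressions were simulated with 12 or 21 items and 100 or 140 surveys, and the same true network in both phases. The strongest significant link into fatigue fell by 20 to 83%, and the pre-post test rejected in 9 to 29%. Over all candidate links the mean change was about 0.000 and the rejection rate 5.2 to 5.6%.

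**Dependence on the true link.** For one link selected only on |z| > 1.96, with a standard error of 0.10 at n = 100:

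| True link | Mean phase I estimate if selected | Mean phase II estimate | Fall |
|---|---|---|---|
| 0 | 0.234 | 0.000 | 100% |
| 0.1 | 0.249 | 0.099 | 60% |
| 0.2 | 0.277 | 0.200 | 28% |
| 0.3 | 0.327 | 0.300 | 8% |
| 0.4 | 0.405 | 0.400 | 1% |

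At n = 140 the falls for 0.2 and 0.3 are 19% and 3%.

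**With a comparator.** If the same rule selects links in both arms and the phase I to II change is compared between arms, false positives return to about 4 to 6%.

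**The case against.** The strongest reply is that {20a} does not say that only advice-related links will be tested. It speaks of the differences between the two networks, and across all links the comparison keeps its nominal error rate. That stands: a reader might infer that the whole network comparison is biased, and it is not. The problem arises when advice-related links are singled out. The mechanism question invites this, and the article sets no safeguard for it.

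Second, selection is not purely statistical. Context, self-knowledge and usefulness count, descriptive figures are used too, the participant's input leads the interpretation, and advice may come from the conversation. This also stands. It dilutes the effect by an amount that the article does not allow one to compute.

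Two stronger readings are not supported. A reader might infer that, combined over participants, a false finding of weakening is nearly certain. But {20a} plans single-subject tests for this objective and {20b} plans no additional analyses, so no pooled test is at issue. A reader might also infer that the bias favours the result the study hopes for. The objectives speak only of exploring changes in the networks; nowhere is weakening named as the desired direction, and a selected link could belong to a helpful factor.

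**Conclusion.** The point holds for links chosen on phase I significance or weight, as a tendency on average and not for every link or participant. Under the stated assumptions, the strongest selected link falls by about 26 to 84% with no true change and is called significantly weaker in about 9 to 29% of single-subject tests. The upper figures belong to weak true links; from about 0.3 to 0.4 upwards the effect is small. The size rests on the assumed spread of true links, the 5% threshold, the choice of the strongest link, independent errors between phases, and least-squares approximations to the planned model.

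This is a minor to moderate point. Objective 3 is exploratory and is pursued only if PROfeel proves effective. The group comparison on the CIS-8 is not affected.

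**What to change.** Add to {20a} that, for advice-related links, the pre-post difference is not interpreted on its own against the phase I estimate that selected them. Write the significance and weight rule down as fixed code. Apply it blind to allocation to the phase I networks of both arms, and compare the phase I to phase II change of the selected links between arms. Fixed code matters here because the statistician who analyses the ESM data also holds the allocation list ({16b}, {16c}, {17a}). The single-subject tests over the whole network can stay as planned.

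The cost is analyst time only, since dietary-first participants complete both ESM phases under Table 1 anyway. There are two limits. The participant's own input to the choice of advice cannot be mirrored in the dietary-first arm, so only the statistical part of the selection is controlled. The reference is also a between-arm summary, so it does not correct any one participant's result.

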### Interim analyses {21b}

Not applicable, no interim analyses will be conducted.

### Methods for additional analyses (e.g., subgroup analyses) {20b}

Not applicable, no additional analyses will be conducted.

### Methods in analysis to handle protocol non-adherence and any statistical methods to handle missing data {20c}

No missing data is expected regarding questionnaires at study visits (KLIK, Eetscore, FFQ, etc.) unless participants drop out of the study. In case of the latter, data will be analyzed up to the point of drop-out. Missing data in the ESM measurement can be handled in the descriptive and dynamic PROfeel reports, e.g., by means of the PDT, although reliability decreases if ESM compliance <70% (see supplement of 41).

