### Criteria for discontinuing or modifying allocated interventions {11b}

This is a minimal risk study. Therefore, we have not specified criteria for discontinuing or modifying allocated interventions. Study participation is voluntary. Participants always have the right to withdraw from participation prematurely at any time, without providing an explanation. The investigator may also withdraw any participant who is unable to complete the QFS-study due to deteriorating health or another reason.

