### Plans to promote participant retention and complete follow-up {18b}

The QFS-study will use multiple strategies to promote that participants do not drop out of the study and complete follow-up. For example, we will minimize the burden of assessments, send reminder letters, emails, or phone calls, provide patients with study team contact information, and combine study visits with usual care visits whenever possible. Study visits will be scheduled as flexible as possible. To enable intention-to-treat analyses, participants who withdraw prematurely from the QFS-study will be encouraged to complete follow-up assessments. Participants’ reasons for withdrawing will be recorded whenever possible.

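### The rule to analyse data only up to drop-out makes the T2 ANCOVA a completer analysis and conflicts with the stated intention-to-treat aim

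*Protocol article*

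**What the plan says.** The missing-data section {20c} expects gaps in visit questionnaires only through drop-out: "No missing data is expected regarding questionnaires at study visits (KLIK, Eetscore, FFQ, etc.) unless participants drop out of the study". It then gives the rule: "In case of the latter, data will be analyzed up to the point of drop-out".

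The retention section {18b} states a different aim: "To enable intention-to-treat analyses, participants who withdraw prematurely from the QFS-study will be encouraged to complete follow-up assessments".

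The first group-level test in {20a} is a "2 × 2 ANCOVA with “fatigue severity” at T2 as dependent variable, “fatigue severity” at baseline as covariate, and intervention condition as fixed factor". The second concerns intervention order: "The second test is a repeated measures 2 × 2 ANOVA to test whether the order in which participants received the advices is of relevance". Its time points are not named. Table 1 places randomisation at T1 (week 5) and the T2 questionnaires at week 17, after the first 12-week intervention.

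On withdrawal, {11b} adds: "The investigator may also withdraw any participant who is unable to complete the QFS-study due to deteriorating health or another reason". The sample size section {14} expects 20% drop-out. Section {18a} has the CIS-8 completed weekly in the smartphone app throughout the study.

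**The concern.** One section collects data after withdrawal so that participants can be analysed as randomised. Another ends the analysis of a participant's data at drop-out. Nothing in the article reconciles the two, so two analysts could follow it in good faith and enter different participants in the main comparison.

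The T2 contrast is the only comparison of the two advices made before everyone crosses to the other one. If it rests on completers, its protection by randomisation depends on drop-out being unrelated to outcome, or related in the same way in both arms. There are reasons not to take that for granted. The investigator knows the allocation and may withdraw a participant for deteriorating health, which may well track fatigue. The two advices also ask for different tasks and different amounts of survey work. If participants who are doing badly leave one arm more often, that arm looks better than it is.

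**Working it through.** **Who is lost from which test**

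- Drop-out between T1 (week 5) and T2 (week 17): there is no T2 value within the {20c} cut-off, so the participant cannot enter an ANCOVA whose outcome is that value.
- Withdrawal before T2 with a T2 score still given, as {18b} encourages: the score lies after the cut-off and on the plain wording is not used.
- Drop-out after T2: the participant stays in the ANCOVA. A conventional repeated measures ANOVA needs every time point it uses, so the participant may be lost from the order test if that test uses T3 or T4.
- The permutation distancing test does not help here. It is offered for the individual-level analysis and for gaps in the ESM data, not for the group-level tests.

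**The plan's own sample size figure**

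Inputs from {14}: alpha 0.05, power 0.80, correlation 0.23, f = 0.5, two arms by two times. For the within or interaction effect, lambda = f² × N × 2 / (1 − 0.23), with 1 and N − 2 degrees of freedom.

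- N = 14: lambda = 0.25 × 14 × 2 / 0.77 = 9.09, power 0.79.
- N = 16: lambda = 0.25 × 16 × 2 / 0.77 = 10.39, power 0.85.

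The smallest even N is 16 per diagnosis group, as stated. Then 16 / 0.80 = 20, and 3 × 20 = 60. The drop-out allowance is correctly computed.

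**Loss of numbers at T2**

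The article does not say when drop-out occurs. If all 20% fell before T2, 0.20 × 60 = 12 would be lost, leaving 48 (24 versus 24 instead of 30 versus 30). This is an upper bound at the expected rate. As an illustration, with a baseline correlation of 0.23 borrowed from {14} and lambda = N × (d/2)² / (1 − 0.23²), the difference detectable with 80% power is 0.72 SD at 30 per arm and 0.80 SD at 24 per arm. This is the loss that the inflation from 16 to 20 was meant to cover, so it is not an extra cost of the rule.

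**Possible bias**

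The inflation does not cover bias. The documents give no drop-out rate by arm. The figures below assume 30% in one arm and 10% in the other (20% overall).

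| Assumption about those who leave | Shift in the T2 contrast |
|---|---|
| They score 0.5 SD worse than completers | (0.30 − 0.10) × 0.5 = 0.10 SD |
| They score 1.0 SD worse than completers | (0.30 − 0.10) × 1.0 = 0.20 SD |
| Exactly the worst outcomes leave | 0.497 − 0.195 = 0.30 SD |
| Propensity to leave correlates 0.5 with outcome | 0.5 × 0.302 = 0.15 SD |

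The third row uses the mean shift of a standard normal after its worst fraction q is removed, φ(z)/(1 − q): 0.3477/0.70 = 0.497 for q = 0.30 and 0.1755/0.90 = 0.195 for q = 0.10.

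With 20% drop-out in both arms and the same difference between leavers and completers, the shift is 0.20 × D − 0.20 × D = 0. If leavers score 0.5 to 1.0 SD worse in one arm only, it is 0.10 to 0.20 SD even with equal rates.

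**The case against.** The strongest reply is that the two sections do not conflict. The article does not define drop-out. If it means the end of all data collection, {18b} maximises what is collected, {20c} covers those who supply nothing more, and nothing is thrown away. Section {18b} also does not name T2 among the assessments it hopes to obtain. This reading is possible, but the text does not state it, and {18b} plainly foresees assessments after withdrawal from the study. Even on this reading, participants with no T2 score fall out of the ANCOVA and no method is given for them.

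Three stronger conclusions are tempting and are not supported:

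- A reader might infer that all drop-outs leave the T2 test, or that 12 lost participants are to be expected there. Only drop-out before T2 counts, and participation runs to week 60.
- A reader might infer that the trial is underpowered because of the rule. The planned inflation already allows for the 20% loss.
- A reader might infer that {20c} discards the weekly CIS-8 scores. It does not: analysing data up to drop-out keeps them, and the rule concerns visit questionnaires. The ANCOVA leaves them out because its outcome is a single value.

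It is also fair that nothing in the article predicts unequal drop-out. Both interventions last 12 weeks, both include boosts from the investigator, and everyone is later allocated to the other advice. Finally, analysis sets and modelling detail are commonly left to a statistical analysis plan, so their absence is not the point. The point is the rule that the article does state.

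**Conclusion.** The point stands in limited form. As written, {20c} combined with the single-value ANCOVA makes the randomised comparison a completer analysis for anyone leaving between T1 and T2. On its plain wording it also sets aside the post-withdrawal scores that {18b} collects for intention-to-treat analysis.

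The loss is at most 12 of 60 at the expected rate and is already allowed for. Bias is possible but not shown: about 0.1 to 0.3 SD under the assumed 30% versus 10% split, where the upper end needs exactly the worst outcomes to leave, and possibly zero if drop-out is similar in both arms. Against a detectable difference of 0.80 SD with 24 per arm, 0.1 to 0.3 SD is roughly one eighth to three eighths (0.10/0.80 = 0.125; 0.30/0.80 = 0.375). This should be fixed, because the wording decides who enters the main test.

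**What to change.** Replace the {20c} sentence with a rule along these lines: all randomised participants are analysed in the arm to which they were allocated, and all collected CIS-8, PedsQL and SES-28 data are used, including assessments completed after withdrawal.

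For participants without a T2 score, estimate the T2 contrast with a method that uses their earlier data. Two reasonable options are a likelihood-based mixed model on the visit values and multiple imputation drawing on the weekly CIS-8 scores already collected. Add one simple sensitivity analysis for data missing not at random. A full model of the weekly series with delta adjustment would also serve but is not required.

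Define drop-out so that stopping the advice, withdrawing from visits and ending all data collection are told apart, and settle the rule before outcome data are examined by arm. Data collection does not change; the cost is wording and slightly more analysis.
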